#### Implementation

To determine if the upgraded helpline is being implemented as intended, a fidelity checklist will be codeveloped with helpline operators and research team ensuring it aligns with the 2022 Australian LBP Clinical Care Standards.^13^ A random audit of 20% of all LBP episodes of care provided following the helpline upgrade will be conducted. Deidentified transcripts of recorded phone calls will be analysed to review the main topics discussed, information and assistance given, and follow-up plans, in accordance with the codeveloped fidelity checks. The proportion of audited calls will be rated as poor, average, good or excellent (based on the codesigned checklist and codefined criteria for each rating). We will also investigate whether there is any association between the fidelity of calls and the time/day the service was delivered or demographics of the callers. In addition, any adaptations to the service or data collection will be recorded and reported. This information will be combined with user-rated acceptability of the helpline, captured as part of the pre–post cohort study questionnaires. A modified version of the TFAQ will evaluate participants’ acceptability of the helpline across several domains including affective attitude, burden, ethicality, intervention coherence, opportunity costs, perceived effectiveness and self-efficacy.^41^

#### Maintenance

At an individual level, maintenance will be evaluated as the impact of the upgraded helpline on self-reported healthcare service use, 6 months following initial contact with the helpline. This will be captured as part of the pre–post cohort study and analysed as per the individual effectiveness outcome. The proportion of callers reporting repeat use (either for the same LBP episode or a new episode) of the helpline service will also be descriptively reported. In addition, cohort participants’ confidence in self-care, measured broadly by the Health Confidence Score,^55^ will be evaluated at 6 months following initial contact. The Health Confidence Score asks participants to rate their knowledge about their health, their ability to self-manage, their ability to navigate the healthcare system and their involvement in decision-making.

At a service level, we will evaluate the sustainability of the upgraded helpline using a mixed-methods approach. This will combine information from qualitative interviews conducted with the cohort participants and two stakeholder focus groups (helpline operators and health service providers), with administrative data on helpline operations (eg, service costs). A minimum of two 1-hour online focus group meetings will be conducted, one for each stakeholder group. Focus groups will explore facilitators and barriers to uptake, effectiveness and sustainability of the helpline.

Cost-effectiveness will be analysed from a health-system perspective utilising the quality-adjusted life-years, based on utility weights from the Assessment of Quality of Life 4D questionnaire^52^ administered at baseline, 3-month and 6-month follow-ups in the preupgrade and postupgrade cohorts. Costs will be identified from self-reported health service use, helpline costs (eg, staff and infrastructure costs) as well as media campaign costs (eg, content development and advertising).

The qualitative insights, stakeholder consultations and cost-effectiveness data will be combined to evaluate the sustainability of the helpline beyond the lifecycle of the research funding. Additionally, the evaluation will establish the feasibility of this model to be scaled up through a broader media campaign (eg, state or national based campaign) and greater integration into Australian primary care.

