### Setting and stakeholders

While the research team will assist with the codesign, implementation and evaluation of the upgraded LBP component of the service, the helpline will continue to be managed and operated by MHA. This free service is currently available to all Australians with telephone access. However, for the purposes of the evaluation, the proposed media campaign will be primarily delivered in the Mid North Coast region—a defined Local Health District, within the state of New South Wales (NSW). The Mid North Coast region has a population of 230 000 broadly reflective of national demographics.^34^ The region was chosen due to its concentrated local media which will enable cost-effective dissemination of media campaign messages and maximise the likelihood of helpline awareness and uptake of the service. Therefore, we anticipate most users of the helpline service and recruited cohort participants will be from that geographical area during the campaign period.

The research partners collaborating on this project include:

MHA, primary research partner and helpline operator. MHA also has an associated consumer advisory committee that works closely with the MHA organisation.Agency for Clinical Innovation, a state-based agency working with consumers, clinicians and partnering with the state Ministry of Health and Local Health Districts to improve health systems within NSW, Australia.Australian Self-Care Alliance, a collaborative organisation of healthcare consumers, health promotion charities, policy experts and industry partners that aim to promote self-care among Australians.Northern Sydney Local Health District (NSLHD) Virtual Care and Hospital in the Home services NSLHD, which manages health facilities, including public hospitals, clinics and healthcare services, provided to the geographical region of Northern Sydney, NSW and also delivers a Virtual Care Service model. The NSLHD will provide expertise on remote care delivery.

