#### Pre–post cohort study participants (from the helpline)

Two independent cohorts (prehelpline and posthelpline upgrade) will be recruited using consecutive sampling of helpline users presenting with a primary complaint of LBP. At the conclusion of their helpline call, helpline operators will verbally invite eligible users to participate in a research study evaluating the helpline service. Interested individuals will receive an electronic information sheet via an online (email or text) REDCap link. Eligible participants will be adults (≥18 years) who are able to provide informed consent for study participation and have sufficient understanding of written and spoken English to read and complete online forms, and have used the helpline service for advice/management of their LBP. Informed consent will be obtained electronically using REDCap’s e-signature feature, prior to research participation in accordance with the institutional ethics approval. Participants can only be enrolled once in the same research period (ie, in the preperiod or postperiod) but can participate in both. Consenting participants will receive an invitation to complete the baseline, 3-month and 6-month questionnaires via REDCap.

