#### Participant-level data

All participant-reported data collection will be conducted externally to MHA by the research team. Data collected from participants will include baseline demographic data (eg, age, sex, education level) from both the preupgrade and postupgrade cohorts, as well as the individuals participating in qualitative interviews or focus groups. For a full list of participant collected data and timepoints, see online supplemental appendix A.

Cohort questionnaires will be administered at baseline (within 10 days of initial helpline service utilisation), 3 and 6 months postinitial service utilisation. All participant collected data will be automatically assigned a unique study identification code and stored and managed using REDCap electronic data capture tools hosted at the University of Sydney.^35 57^ Qualitative data collected during interviews, including transcripts of interviews, will be stored in a password-protected folder in the highly protected SharePoint folder hosted by the University of Sydney. Only designated research team members will have access to this data.

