A comparison of primary participant-reported outcome (self-reported healthcare service utilisation) and secondary outcomes, between the preupgraded and postupgraded helpline cohorts will be conducted. The primary outcome will be analysed at 3 months (as part of the effectiveness dimension) and 6 months (as part of the maintenance dimension). Healthcare service use will be collected as count data and analysed using negative binomial regression model. The rate ratio will be estimated comparing the postupgrade cohort to preupgrade cohort. Negative binomial regression will account for individual follow-up time and potential overdispersion due to non-independence of repeated measures. Matching with replacement will be used to address potential imbalances between cohorts in baseline demographics and to account for the anticipated smaller ‘unexposed’ preupgrade cohort compared with the larger ‘exposed’ postupgrade cohort. Sensitivity analyses will be conducted to assess the robustness of the findings.

Individual qualitative interviews will be conducted with purposively selected cohort participants to identify factors and processes that contributed to the helpline uptake, implementation and future scalability. These include acceptability and appropriateness (the extent to which the helpline is perceived as agreeable and relevant); advertising campaign effectiveness; individual factors (eg, participants’ socioeconomic status); and service outcomes (eg, the extent to which the helpline is perceived to be effective, patient centred, timely). Interviews will be semistructured, using a mixture of inductive and deductive thematic analysis drawing on the PRISM framework.^36^ An interview guide will be used to ensure the same topics are explored across individual interviews.

Focus groups with key stakeholder groups will be conducted online to identify factors and processes that contributed to helpline uptake, implementation and future scalability. The interview guide will be informed by findings from the implementation phase to align with observed barriers and enablers. Focus group data will be analysed using a combination of inductive and deductive approaches, drawing on the PRISM framework to guide interpretation.

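### The only stated adjustment between the two non-randomised cohorts is matching on demographics, which does not balance baseline AQoL-4D utility or baseline secondary scores

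*Protocol article*

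**What the plan says.** The Maintenance section plans a cost-effectiveness analysis from a health-system perspective, "utilising the quality-adjusted life-years, based on utility weights from the Assessment of Quality of Life 4D questionnaire". The questionnaire is "administered at baseline, 3-month and 6-month follow-ups in the preupgrade and postupgrade cohorts". That section names no QALY estimator, regression model or covariate list.

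On design, the recruitment section states: "Two independent cohorts (prehelpline and posthelpline upgrade) will be recruited using consecutive sampling of helpline users presenting with a primary complaint of LBP". The Setting and stakeholders section adds a likely shift in who is recruited: "we anticipate most users of the helpline service and recruited cohort participants will be from that geographical area during the campaign period".

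The Effectiveness section lists quality of life among the secondary outcomes. The cohort paragraph in Data analysis covers the primary outcome and also "secondary outcomes, between the preupgraded and postupgraded helpline cohorts will be conducted". For imbalance it offers one named remedy: "Matching with replacement will be used to address potential imbalances between cohorts in baseline demographics". It closes with a general line: "Sensitivity analyses will be conducted to assess the robustness of the findings".

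The Participant-level data section illustrates baseline demographic data by age, sex and education level, and fixes the timing: "Cohort questionnaires will be administered at baseline (within 10 days of initial helpline service utilisation), 3 and 6 months postinitial service utilisation".

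**The concern.** Two cohorts recruited in different periods, one of them largely after a regional media campaign, may differ in how unwell callers are when they ring. Demographic matching addresses age, sex and similar traits. It balances health status only so far as health status follows those traits.

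For most outcomes this is ordinary confounding. For a QALY computed as an area under the curve there is a further step: the baseline utility is an arithmetic component of the outcome, and the 3- and 6-month utilities are likely to be correlated with it. A baseline gap therefore passes into the between-cohort difference, even if the service changed nothing.

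The QALY difference is the denominator of a cost-effectiveness ratio. The Maintenance section feeds the cost-effectiveness results, with qualitative and stakeholder evidence, into the judgement on sustainability and scale-up. The same weakness, without the arithmetic component, applies to the other secondary scores that have a baseline value.

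**Working it through.** **Inputs from the protocol article.** Utilities at 0, 3 and 6 months (Maintenance). About 50 preupgrade participants; 208 postupgrade completers, inflated for 15% loss (Effectiveness).

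**The plan's own figure.** 208 / (1 − 0.15) = 244.7, rounded up to 245; 50 + 245 = 295. Both reproduce. The article gives no QALY, utility or utility SD figure to check.

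**Assumptions.** QALYs by the trapezoid rule; a fraction r of the baseline gap persists at both follow-ups without any service effect; true utility gain d equal at 3 and 6 months; utility SD 0.20 to 0.30.

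**Step 1, weights.** Each interval is 0.25 years.

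QALY = 0.25 × (u0 + u3)/2 + 0.25 × (u3 + u6)/2 = 0.125·u0 + 0.25·u3 + 0.125·u6

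The weights sum to 0.5 years.

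**Step 2, carry-over of a baseline gap g.** The spurious QALY difference is g × (0.125 + 0.375r):

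| Gap g | r = 0 | r = 0.5 | r = 0.7 | r = 1 |
|---|---|---|---|---|
| 0.02 | 0.0025 | 0.0063 | 0.0078 | 0.010 |
| 0.05 | 0.0063 | 0.0156 | 0.0194 | 0.025 |
| 0.10 | 0.0125 | 0.0313 | 0.0388 | 0.050 |

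**Step 3, a real effect.** A true gain d at 3 and 6 months adds 0.375 × d: 0.01125 QALYs for d = 0.03, and 0.01875 for d = 0.05.

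**Step 4, gap that equals a real effect.** g = 0.375d / (0.125 + 0.375r):

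| True gain d | r = 0 | r = 0.5 | r = 0.7 | r = 1 |
|---|---|---|---|---|
| 0.03 | 0.09 | 0.036 | 0.029 | 0.0225 |
| 0.05 | 0.15 | 0.06 | 0.048 | 0.0375 |

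**Step 5, how large a gap chance alone gives.** SE = SD × √(1/50 + 1/245) = 0.031, 0.039 and 0.047 for SD 0.20, 0.25 and 0.30. The probability of an absolute gap above 0.05 is then about 11%, 20% and 28%. A gap of that size is possible by chance but not likely. A systematic change in case mix would come on top, and the article gives no basis for estimating it.

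**Step 6, effect of the covariate.** With baseline utility in a correctly specified linear model, the part of the QALY difference due to the baseline gap falls to about zero. For a gap of 0.05 that removes 0.0063 (r = 0) to 0.025 (r = 1) QALYs. Confounding not captured by baseline utility remains.

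**The case against.** The strongest reply is that the article fixes no QALY model. Collecting the utility at baseline in both cohorts is what adjustment needs, and covariates for an economic analysis are commonly left to a statistical or health-economic plan, which is not shown. This stands. A reader might infer that the plan compares QALYs without baseline utility, or collects it and does not use it; no section says so.

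The reply does not dispose of the point, because Data analysis is not silent on adjustment. For the cohort comparison of primary and secondary outcomes it names a remedy and says what that remedy targets. The item that section expressly defers to the statistical analysis plan is the form of the media campaign's impact, not the cohort covariates.

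A second reply is that the article uses demographic loosely: the Secondary data section counts pain severity and physical activity under that word. This weakens any claim that clinical severity is shut out of the matching. It does not bring in baseline utility or baseline scores, which no section mentions for this purpose. The promised sensitivity analyses are unspecified.

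Third, chance imbalance is sampling error that an unadjusted confidence interval already reflects; only a systematic gap biases the contrast. This is correct. A reader might infer that about 50 preupgrade participants make a sizeable gap likely by chance alone; step 5 does not support that.

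Fourth, a reader might credit the covariate with raising power from 80% to about 99%. The documents do not support this figure: the 80% in the Effectiveness section belongs to healthcare-use counts, and no QALY contrast is powered.

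Finally, the Discussion already concedes that causal inference is limited without randomisation. That does not excuse leaving a measured and removable imbalance to chance.

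**Conclusion.** The point holds as a weakness in the stated adjustment, not as a demonstrated omission from the QALY model. Followed as written, demographic matching leaves a baseline utility gap in the quality-of-life and QALY contrasts.

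On size: if half or more of the gap persists (r = 0.5 to 0.7), a gap of about 0.03 to 0.04 gives as large a QALY difference as a true utility gain of 0.03. If none persists, 0.09 is needed. This rests on area-under-the-curve QALYs and on assumed persistence and gain, none of which the article states. Whether such a gap will occur is unknown. The design gives reason to expect differing case mix, but the article does not quantify it.

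The consequence is limited to the secondary outcomes and the economic analysis, which is one of several inputs to the scale-up judgement.

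**What to change.** In the cost-effectiveness paragraph of Maintenance, state that the QALY difference between cohorts will be estimated with baseline AQoL-4D utility as a covariate, alongside the demographic matching. In Data analysis, state that each secondary score with a baseline measurement will be compared with its own baseline value as a covariate. In both places, report the estimate without this covariate next to the adjusted one.

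The cost is a sentence or two in each section; for the QALY comparison no new data are needed. There are two small downsides. Participants with a missing baseline value need a stated handling rule to stay in the model. And because the baseline questionnaire may be completed up to 10 days after first helpline contact, adjusting for it could remove some early effect of the service; showing both estimates lets the reader see how far the covariate moves the result.

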### Media campaign

To increase reach, awareness, service use and potential impact of the upgraded helpline, a targeted mass media campaign will be conducted. Mass media campaigns use media sources such as radio, television and social media to disseminate information/messages to a large audience.^42^ Previous studies suggest that this method can effectively promote and increase calls to helpline services.^42^,^44^ The campaign messaging will be codesigned with consumers, the research team and a dedicated advertising agency to create a campaign strategy that aligns with the objectives of MHA’s helpline and the objectives of the partnership project. The media campaign content will be created in consultation with a professional content creation company and reviewed by the research team, partner organisations and consumers prior to launch.

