#### Reach

Reach will be assessed to determine the extent to which the media campaign raises awareness of the helpline and influences service utilisation. This will be evaluated using two approaches:

(1) To evaluate media campaign reach, we will conduct population-based surveys in the ‘intervention’ region (the Mid North Coast Local Health District of NSW) targeted by the campaign, and a ‘control’ region (Southern NSW Local Health District) that will remain unexposed to the media campaign. The control region was chosen for its similarity in population size and distribution to the intervention region, as well as the geographical distance of approximately 450 km and different media markets, which are expected to minimise campaign crossover. Surveys will be administered online via a commercial panel company. The survey will include a single campaign awareness question assessing recognition of the helpline service along with basic aggregated demographic information (eg, age group, sex and postcode) to enable region comparisons. Surveys will be conducted at baseline (precampaign) and postcampaign to measure population awareness of the helpline. Sample size calculations are based on the postcampaign comparison between the two regions (baseline awareness will be summarised descriptively). Based on feasible sample sizes provided by the panel company, a total of 300 respondents in the intervention region and 400 in the control region will be surveyed at both time points. Assuming 0.05% of respondents are aware of the helpline in the control group, this provides 85% power to detect a 3% difference in awareness between regions at a two-sided significance level of 5%.

(2) To evaluate the impact of the campaign on service use, we will analyse the monthly call rates using retrospective data to compare the rates of unscheduled calls with a primary complaint of LBP. This will be analysed 18 months before and 12 months after the campaign begins. An interrupted time series design will be used to determine the effect of the media campaign on call volume.

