#### Effectiveness (primary intervention outcome)

The effectiveness of the helpline service will be evaluated at both an individual participant and population (health district) level.

Participant-level effectiveness will be evaluated using a pre–post cohort study. The primary outcome to assess individual effectiveness will be self-reported healthcare use (eg, general practitioner and imaging usage). This will be compared between an independent cohort of participants with a primary complaint of LBP who use the original service, and an independent cohort who use the upgraded service. The primary outcome will be analysed 3 months post service initiation. Cohort participant questionnaires will also capture secondary outcomes including pain intensity,^50^ disability,^51^ quality of life,^52^ the validated single-item physical activity question,^53^ two-item pain self-efficacy,^54^ health confidence score^55^ and acceptability.^41^ Based on historical service volume data from the MHA helpline, we anticipate approximately 50 participants in the preupgrade period and will require a minimum of 208 participants in the postupgrade period to detect an event rate difference of 4 healthcare service utilisations between the preupgrade and postupgrade cohort, with 80% power and 5% type-1 error rate. This is the equivalent of a 40% difference based on an average health service utilisation rate of 10 services per participant over 12 months observed in unpublished work.^56^ Adjusting for a loss to follow-up of 15% in the postupgrade cohort, we will require 245 participants postupgrade to achieve the required 208 completers. Combined with the anticipated preupgrade cohort, the total sample size is 295 participants.

Population effectiveness will be evaluated using aggregated Local Health District data on ED presentations for patients with a complaint of LBP. The analyses will be restricted to the Mid North Coast Local Health District (or relevant hospitals) data corresponding with the location of the media campaign. An interrupted time series design will be used to analyse the monthly change in LBP presentation rates and any associated trend change following the introduction of the media campaign.

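### The cost-effectiveness inputs include the media campaign's cost, but QALYs come only from a comparison of helpline users with helpline users, so the ratio values neither the upgrade alone nor the campaign

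*Protocol article*

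**What the plan says.** All of the following is in the protocol article.

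- **Perspective and measure (Maintenance):** "Cost-effectiveness will be analysed from a health-system perspective utilising the quality-adjusted life-years".
- **Effect (Maintenance):** utility weights come from a quality-of-life questionnaire "administered at baseline, 3-month and 6-month follow-ups in the preupgrade and postupgrade cohorts".
- **Costs (Maintenance):** self-reported health service use, together with "helpline costs (eg, staff and infrastructure costs) as well as media campaign costs (eg, content development and advertising").
- **Who is in the cohorts (Pre–post cohort study participants):** "Two independent cohorts (prehelpline and posthelpline upgrade) will be recruited using consecutive sampling of helpline users presenting with a primary complaint of LBP".
- **Comparator (Effectiveness):** an "independent cohort of participants with a primary complaint of LBP who use the original service", set against a second cohort using the upgraded service.
- **Purpose of the campaign (Media campaign):** "To increase reach, awareness, service use and potential impact of the upgraded helpline, a targeted mass media campaign will be conducted".
- **Where the campaign's effect is measured:** the Reach section states "An interrupted time series design will be used to determine the effect of the media campaign on call volume". The Effectiveness section adds a time series of emergency department presentations in the campaign district. The cost-effectiveness paragraph names neither as an input.
- **Timing (Testing and refinement):** an estimated 50 people who use the upgraded service before the campaign become the first members of the postupgrade cohort.
- **Use of the result (Maintenance):** it is combined with qualitative and stakeholder findings to judge sustainability. The evaluation is also to establish whether the model can be scaled up through a wider campaign.

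**The concern.** The cost side and the effect side describe different decisions. The costs are those of upgrade plus campaign. The QALY difference is that of the upgrade alone, among people who called.

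The campaign exists mainly to bring in people who would otherwise not have called. For them the alternative is no helpline, and no group without helpline contact supplies utilities or costs.

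Cost-effectiveness belongs to the project's third aim, and the fourth aim is a plan for national deployment if the service proves effective. Part of that decision is whether to buy more campaign. A ratio that charges for the campaign without valuing the callers it adds does not inform that choice. It also obscures whether the upgrade is worth its cost for each caller.

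**Working it through.** The article states no campaign cost, QALY gain or cost-effectiveness ratio, so there is no figure to reproduce. The check is structural, followed by algebra on the direction of the error.

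**Step 1. Terms, per campaign-period caller**

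- u: extra cost of upgraded over original service
- c: campaign cost
- q1: QALY gain of upgraded over original service
- s: net cost of the original helpline against no helpline
- q0: QALY gain of the original helpline against no helpline
- f: share of callers who call only because of the campaign

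The cohorts can estimate q1, and u with the helpline cost data. Campaign accounts give the total behind c, and the call-rate time series informs f. Nothing planned measures s or q0.

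**Step 2. Three ratios**

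- From the stated inputs, with helpline cost taken as a per-user difference: (u + c) / q1.
- Upgrade alone: u / q1.
- Whole programme (upgrade plus campaign, against original service without campaign): callers who would have called anyway contribute u and q1; added callers contribute u + s and q1 + q0. The ratio is (u + c + f·s) / (q1 + f·q0).

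The first equals the second only if c = 0. With f above zero it equals the third only if s/q0 = (u + c)/q1.

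**Step 3. What is missing**

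Added callers gain f·(q1 + q0) against no helpline. The cohort comparison credits f·q1 and leaves out f·q0. Under per-user costing it also leaves out f·s.

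**Step 4. Direction**

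Dividing the stated-input ratio by the programme ratio gives

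(1 + f·q0/q1) / (1 + f·s/(u + c)).

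With q1, q0 and u + c positive, this exceeds 1 (error against the programme) only if s/q0 is less than (u + c)/q1.

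Illustration with assumed values only: u = A$100, c = A$300, so u + c = A$400; q1 = 0.01.

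| f | s | q0 | Calculation | Stated / programme |
|---|---|---|---|---|
| 0.50 | A$50 | 0.01 | 1.5 / 1.0625 | 1.41 |
| 0.50 | A$50 | 0.005 | 1.25 / 1.0625 | 1.18 |
| 0.50 | −A$50 | 0.005 | 1.25 / 0.9375 | 1.33 |
| 0.50 | A$50 | 0.00125 | 1.0625 / 1.0625 | 1.00 |
| 0.50 | A$50 | 0 | 1 / 1.0625 | 0.94 |
| 0.75 | A$50 | 0.01 | 1.75 / 1.09375 | 1.60 |
| 0.75 | A$50 | 0 | 1 / 1.09375 | 0.91 |

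The error can go either way. If the net cost of added callers were charged in full while their gain over no helpline stayed out, the quotient would be 1 + f·q0/q1, which is never below 1. The costing rule therefore matters too, and the article does not give it.

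**Step 5. Participants enrolled before the campaign**

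208 / (1 − 0.15) = 244.7, rounded up to 245, which matches the article. Of these, about 50 enrol before the campaign: 50 / 245 = 20%. The campaign cannot have brought them in, so the postupgrade cohort is not a cohort of campaign-period callers either.

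**The case against.** **The article fixes no ratio.** It lists where costs will be found. It gives no base case, apportionment rule or denominator, and does not exclude a result without campaign cost. A condensed article may leave these to a fuller economic plan. That stands, and their absence is not part of this point. But no apportionment rule supplies the missing comparison with no helpline, because the described design does not collect it.

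**Counting campaign cost is legitimate.** The second aim pairs the upgrade with its promotion, and scale-up would involve a wider campaign. This also stands. It argues for showing results with and without campaign cost, not for banning it from the base case.

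**The decision does not rest on one ratio.** Qualitative findings, call volume and emergency department trends are reported as well. This lowers the stakes but does not repair the ratio.

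**Stronger readings a reader might infer.** One is that the campaign's benefit is wholly absent. It is not: campaign-period callers are in the postupgrade cohort, and the Setting and stakeholders section expects most participants to come from the campaign area. Their gain from upgraded over original service is counted; only the gain of the original service over no helpline is lost. Another is that the ratio is certainly biased against the programme. The documents do not support this, because the cost of serving added callers may also be missing and the sign turns on s and q0, which are not given. Differences in case mix between campaign-recruited and earlier callers could push either way. Nor can the error be put in dollars per QALY: the campaign cost, the QALY gain and the number of callers sharing that cost would all have to be invented.

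**Conclusion.** The mismatch holds. The Maintenance section counts campaign cost, while its only QALY comparison sets helpline users against helpline users. A ratio from those inputs answers neither the upgrade question nor the campaign question.

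The direction is not determined by the documents. Under per-user costing the error is against the programme if the original helpline's own net cost per QALY against no helpline is below the planned ratio, as it would be if that service helps at low net cost. It is nil or in the programme's favour if the original helpline adds little or nothing. The range of 0.91 to 1.60 rests wholly on assumed inputs; it shows that the sign can change and does not estimate the error.

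This is a secondary analysis, but it feeds the scale-up judgement, and most of the repair is wording.

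**What to change.** In the cost-effectiveness paragraph of the Maintenance section:

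1. Report upgraded versus original service per caller, using health service use and helpline costs without campaign cost, alongside any result that includes campaign cost.
2. Report the campaign separately as campaign cost divided by additional LBP calls, taking the additional calls from the interrupted time series in the Reach section.
3. Present any combined programme ratio as a scenario. State and vary the apportionment of campaign cost over all campaign-period callers, the service cost of added callers, and the outcome without a helpline.

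The first two items need only data already planned. The cost is that there is more than one economic result to report. The combined scenario will rest on values for the no-helpline state that nobody in this study measures, and it should be labelled so.
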